**Data collection and management**

Data will be collected at baseline, 6 weeks and at the final 12-week assessment and stored via REDCap. Baseline data will include demographic information, medical history, weight (kg), height (cm), body-mass index (BMI), oral hygiene practices, and oral hygiene knowledge associated with CVD. CEAP nurses record weight, height, and BMI when patients first attend the program, as such this data and other required medical data will be retrieved from participant clinical records. Questionnaires delivered via REDCap via iPads. Clinical parameters will be recorded at baseline, the 6-week, and the final follow-up after 12 weeks. PSR, SBI, and API will be completed using a disposable World Health Organisation (WHO) periodontal probe and mirror, with tricolour disclosing gel. For timeline and mode of collection see **Table 1**.

Each site will hold a master spreadsheet held on WSLHD servers. Identifiable data including name, address and phone numbers will be housed on secure servers within the WSLHD network. The server is managed and maintained by WSLHD Digital Health Services (DHS). Each patient will be assigned a code – the patient’s name and dental record number will be linked to the study code and stored in an encrypted and password protected folder, separate to all other data files, with access to this folder limited to the principal investigator and coordinating principal investigator. All other data files will contain only the study code. Participant consent forms will be in digital form as part of REDCap, thus stored electronically. Data sheets will contain the study code, age and sex and will be stored electronically. De-identified data will be used for any analyses and publications and all data collected during the study will be retained for a period of 5 years following the study completion. We anticipate no harm resulting from the intervention, as such we do not require a data safety monitoring board.

**Table 1.** Timing and mode of collection of study data

| Measurements and Surveys | Baseline | 6-week  Assessment | 12-week  Final Assessment |
| --- | --- | --- | --- |
| Demographic information and medical history and behaviour/risk factors | X |  |  |
| Clinical measurements PSR/API/SBI | X | X | X |
| Oral health Perceptions and knowledge | X | X | X |
| Oral hygiene habits | X | X | X |
| Motivation and confidence and to improve oral hygiene practices | X | X | X |
| Perceptions of nurses involvement oral health care | X |  |  |
| Do they have an oral health practitioner and see them regularly | X |  |  |
| Perceived value of their oral health | X | X | X |
| Motivation to see oral health practitioner | X | X | X |
| *Perception of cardiac nurses of importance and effectiveness of the intervention – delivered to nurses at study completion. | | | |

**Clinical measurements**

API and SBI are a rapid way of assessing and monitoring a patient’s oral hygiene (81,83). Using the WHO periodontal probe again, SBI is completed by gently inserting the probe into the interproximal areas of the buccal sulcus of the first and fourth quadrant, and palatal/lingual sulcus surfaces of the second and third quadrant. Any evidence of bleeding on probing (BOP) is recorded. Next, API is completed. Using a micro brush, place a small amount of the disclosing liquid on and around the interdental papilla of each tooth. This occurs on the buccal surfaces of the second and third quadrants, and the lingual/palatal surfaces of the first and fourth quadrants. After allowing the patient to rinse, interproximal sites that have any remaining disclosing solution is recorded as a positive reading.

Assessing oral hygiene using SBI and API requires a percentage to be calculated. See **Table 2** for API/SBI percentage results. For the SBI percentage, divide the number of positive BOP sites by the number of total tooth sites and times by 100. To work out API percentage divide the number of positive disclosing sites by number of tooth total sites, and times by 100. This will be completed at baseline and at the 6 and 12-week follow ups where percentages will be compared for any differences. Once an oral hygiene routine has been implemented, improvements can be confirmed as early as 2 weeks (85).

PSR is also a rapid assessment of a patient’s periodontal health (86). It is completed systematically by dividing the mouth into sextants and, starting in sextant one, gently inserting a WHO periodontal probe into the gingival sulcus taking a 6-point measurement of each tooth. Specific markings on the probe relates to a measurement, indicating to the OHP which code to classify the sextant as, and if a full periodontal screening and analysis should be performed. See **Table 3** for code definitions. Any participants returning a PSR code of 3 or 4 will still be included in the study, however, will be strongly advised to seek an OHP for further assessment.

**Sample size**

The required sample size for this study is calculated to be a total of 165 (1:1:1 Group A: Group B: Group C). This calculation includes provision for a 10% attrition rate, two tailed tests, type 1 error of 5%, and will have 80% power to detect any significant difference between Group A and Group C. This calculation is based from an API score reduction of 25% in the intervention arm of Ziebolz, et al 2009 study (87). However, due to our exclusion criteria of ≤59% API score, we will expect to see a 40% decrease in Group A, compared to 15% in Group C. This current study is powered to detect a difference in percentage proportion of those between Group A and Group C however, has poor power to detect a difference between Group B and Group C.

| Table 2. Adapted API/SBI measurement results (88) | | |
| --- | --- | --- |
|  | **API** | **SBI** |
| Poor oral hygiene | >35% | >25% |
| Fair oral hygiene | 35% | 15-25% |
| Good oral hygiene | <25% | <15% |

| Table 3. Adapted PSR code definitions (86,89). | |
| --- | --- |
| Code | Clinical Signs |
| 0 | Absence of clinical signs: no calculus, or BOP  Coloured band on WHO probe completely visible. |
| 1 | No calculus.  BOP  Coloured band on WHO probe completely visible. |
| 2 | Supra and/or subgingival calculus  BOP  Coloured band on WHO probe completely visible. |
| 3 | Periodontal pocket 3.5mm-5.5mm  Coloured band on WHO probe partially visible |
| 4 | Periodontal pocket >5.5mm deep  Coloured band on WHO probe no longer visible |
| X | Sextant absent of dentition |
| * | Periodontal abnormalities which include:  Furcation involvement  Mobility  Mucogingival problems for example: exudate, severe oedema  >3.5mm recession  The * is recorded next to the sextant number code. E.g. “3*” |

**Statistical analysis**

The statistical plan for this study will be determined prior to study completion. Analysis of the difference in API will be according to the intention-to-treat principle where participants are analysed in the arm they have been allocated. The level of statistical significance will be set at p-value <0.05. The primary analysis will be an adjusted analysis of variance performed to assess differences between groups for API scores between baseline and follow-up. Covariates used for adjusted analyses will include age, sex, highest PSR code, level of education, smoking status, and number of teeth. Subgroup analysis of the intervention effect and age, sex, education, ethnicity, and cardiovascular disease presentation (coronary heart disease, heart failure, heart transplant list, heart transplant receiver) will also be explored. Outcome measures available at baseline (PSR, SBI and API) will also be included in the statistical model. An unadjusted analysis will be performed to assess differences between groups using a X^2^ test for binary (categorical) outcomes and independent sample t-tests for continuous outcomes.

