The primary outcome of this study is to determine if individualised OHI combined with DOHE improves approximal plaque index (API) (81) scores between baseline and the 6-week follow-up, compared with usual care/no OHI education. Secondary outcomes of this study will determine if digitally delivered oral health education alone or partnered with individualised OHI improves API scores between baseline and the 12-week follow-up, compared with usual care. It will compare the mean reduction of API and SBI between each group at baseline and follow up, and determine if any participant reaches scores that are clinically significant. It will assess any changes to patients’: motivation, confidence, and behaviour regarding their oral hygiene practices, knowledge of oral health impacts on cardiovascular health, as well as their experience with oral care whilst on the ward. Additionally, it will assess the cardiac nursing staff views on an oral health education program within the rehabilitation facility. As good oral hygiene habits are an upstream approach of reducing risk of systemic chronic inflammation, and as such, risk of a future cardiac event (29), we hypothesise introducing an individual OHI partnered with DOHE program into the cardiac rehabilitation out-patient clinic will help improve API scores between baseline and follow-up. We also hypothesise the program will increase patients’ awareness of the impact of oral health on cardiovascular health and help to motivate and give them confidence in caring for their oral health; and if not doing so already, incorporating regular visits to an OHP.

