**Study outcomes**

Primary outcome

The primary outcome of this study is to show the percentage of participants reducing their API score ≥40% after 6 weeks, compared to baseline is higher in Group A than in Group C.

Secondary outcomes

The secondary outcomes of the study will be:

- To show the percentage of participants reducing their API score by ≥40% after 12 weeks, compared to baseline, is higher in Group A (OHI & DOHE) than in Group C (usual care/no oral hygiene intervention).
- To show the reduction in mean API score after 6 weeks, compared to baseline, is higher in Group A (OHI & DOHE) than in Group C (usual care/no oral hygiene intervention).
- To show the reduction in mean API score after 12 weeks, compared to baseline, is higher in Group A (OHI & DOHE) than in Group C (usual care/no oral hygiene intervention).
- To show the reduction in mean API score after 6 weeks, compared to baseline, is higher in Group A (OHI & DOHE) than in Group B (DOHE).
- To show the reduction in mean API score after 12 weeks, compared to baseline, is higher in Group A (OHI & DOHE) than in Group B (DOHE).
- To show the reduction in mean API score after 6 weeks, compared to baseline, is higher in Group B (DOHE) than in Group C (usual care/no oral hygiene intervention).
- To show the reduction in mean API score after 12 weeks, compared to baseline, is higher in Group B (DOHE) than in Group C (usual care/no oral hygiene intervention).
- To show the reduction in mean SBI score after 6 weeks, compared to baseline, is higher in Group A (OHI & DOHE) than in Group C (usual care/no oral hygiene intervention).
- To show the reduction in mean SBI score after 12 weeks, compared to baseline, is higher in Group A (OHI & DOHE) than in Group C (usual care/no oral hygiene intervention).
- To show the reduction in mean SBI score after 6 weeks, compared to baseline, is higher in Group A (OHI & DOHE) than in Group B (DOHE).
- To show the reduction in mean SBI score after 12 weeks, compared to baseline, is higher in Group A (OHI & DOHE) than in Group B (DOHE).
- To show the reduction in mean SBI score after 6 weeks, compared to baseline, is higher in Group B (DOHE) than in Group C (usual care/no oral hygiene intervention).
- To show the reduction in mean SBI score after 12 weeks, compared to baseline, is higher in Group B (DOHE) than in Group C (usual care/no oral hygiene intervention).
- Assess the percentage in each Group that has reached clinically significant API scores of ≤35%.

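### The stated primary analysis, an adjusted ANOVA of API scores, does not test the declared and powered primary outcome, the 6-week responder proportion in Group A versus Group C

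*Protocol*

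**What the plan says.** **Primary outcome (Protocol, Study outcomes).** The aim is to show that "the percentage of participants reducing their API score ≥40% after 6 weeks, compared to baseline is higher in Group A than in Group C". This fixes a binary endpoint, one visit and one contrast. The reduction in mean API, A versus C at 6 weeks, is listed separately as a secondary outcome.

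**Sample size (Protocol, Sample size).** The trial is described as "powered to detect a difference in percentage proportion of those between Group A and Group C", with 165 participants randomised 1:1:1, two-sided 5% type 1 error, 80% power, 10% attrition, and expected figures of 40% in Group A and 15% in Group C.

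**Analysis (Protocol, Statistical analysis).** The sentence that names a primary analysis is: "The primary analysis will be an adjusted analysis of variance performed to assess differences between groups for API scores between baseline and follow-up". It has no responder threshold, and it names neither the A versus C contrast nor the visit. The method for binary outcomes comes at the end of the section: "An unadjusted analysis will be performed to assess differences between groups using a X^2^ test for binary (categorical) outcomes". That test is not called primary.

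**Aims (Protocol, last paragraph of the introduction, under Oral health promotion studies).** The primary outcome is worded as whether the intervention "improves approximal plaque index (API) (81) scores between baseline and the 6-week follow-up", again without a threshold.

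**The concern.** A protocol may leave the method of its primary analysis to the SAP. This one does not: it names a primary analysis, and that analysis has a different dependent variable from the primary outcome. An SAP that follows the Statistical analysis section departs from the Study outcomes and Sample size sections, and an SAP that follows those two departs from the Statistical analysis section.

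What is at stake is which p-value decides the trial. Read literally, the trial would be decided on what the protocol lists as a secondary outcome, using a test for which no power was calculated. The chi-square test of responders would sit beside it as a second candidate. The means test will usually be the more sensitive of the two, so the likely conflict is a significant difference in means beside a non-significant difference in responders.

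**Working it through.** **1. Reproducing 165.** Inputs from the Sample size section: p_A = 0.40, p_C = 0.15, two-sided alpha 0.05 (z = 1.960), power 80% (z = 0.842), attrition 10%, three equal arms.

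Pooled-variance formula without continuity correction, with p̄ = (0.40 + 0.15)/2 = 0.275:

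n = [1.960·√(2·0.275·0.725) + 0.842·√(0.40·0.60 + 0.15·0.85)]² / 0.25² = [1.238 + 0.510]² / 0.0625 = 48.9, so 49 per arm.

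49/0.90 = 54.4, so 55 per arm, and 3 × 55 = **165**, exactly as stated.

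Other versions of the calculation give different totals:

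| Version | Total |
|---|---|
| Unpooled variance | 159 |
| Continuity-corrected | 192 |
| One-sided | 132 |
| Attrition added as 49 × 1.1 | 162 |

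With 49 evaluable per arm the power for 40% versus 15% is 80.1% (exact power of the uncorrected chi-square test, 80.9%). The stated 80% is the power of the responder comparison.

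**2. Power of the stated ANOVA.** It cannot be computed, because the protocol gives no SD for API. For a 25-point mean difference with 49 per arm, power by assumed SD is:

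| SD | Power |
|---|---|
| 20 | >99.9% |
| 30 | 98.5% |
| 40 | 87.2% |
| 44 | 80.3% |

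A comparison of means would need 49 per arm only at an SD of about 44, a figure the protocol never states.

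**3. How far the two tests can differ, with 40% and 15% as responder rates.** Assume normal API changes with equal SD. Rates of 40% and 15% above a common cut imply a standardised mean difference of 1.036 − 0.253 = 0.783. Power of the means test with 49 per arm: 0.783·√(49/2) − 1.960 = 1.916, and Φ(1.916) = 97%. In 20,000 simulated trials:

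- the responder test was significant in 81% and the means test in 97%;
- they disagreed in 17.3%: means test only in 16.9%, responder test only in 0.4%.

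**4. The other reading, with 40 and 15 as mean decreases.** Assume normal changes with means 40 and 15, a responder cut at 40 points and 49 per arm. This gives 50% responders in Group A and a Group C rate that depends on the SD. The disagreement by simulation is:

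| Assumed SD | Trials in which the tests disagree |
|---|---|
| 20 | under 1% |
| 25 | 4% |
| 30 | 11% |
| 35 | 18% |
| 40 | 23% |

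The larger SDs fit the scale poorly. Entry requires API above 59% and API cannot exceed 100%, so a rise cannot exceed 41 points. At SD 40 the model places Φ((−41 − 15)/40) = Φ(−1.4) = 8% of Group C beyond that limit, and Φ(−60/40) = 7% of Group A at falls of more than 100 points.

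**The case against.** The best defence is that the Study outcomes section already settles endpoint, visit and contrast, that the Statistical analysis section does supply a chi-square test for binary outcomes, and that an SAP can tie the two together. Part of this stands, and it rules out several stronger readings.

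- **That the primary outcome is never tested.** A reader might infer this, but the chi-square sentence covers it. The defect is one of designation: the fitting test is labelled unadjusted and is not primary.
- **That a three-arm omnibus F-test would decide the trial and could reject because of Group B alone.** The protocol does not specify an omnibus test. Its unadjusted method for continuous outcomes is the pairwise t-test, and the A versus C contrast is fixed elsewhere. Detail on contrast and visit may properly be in the SAP.
- **That the analysis will be chosen once results are visible.** The protocol says the plan will be determined before study completion. That is an outer limit; it allows earlier finalisation and says nothing about access to results by arm. Nothing documents that 6-week data will have been seen.
- **That the aims paragraph is a rival definition.** It names the same visit and the usual-care comparator. It is looser wording that should be aligned, and little more.
- **That the tests would disagree in at least one trial in six.** That holds only under particular assumptions and fails at smaller SDs.

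What the defence does not remove is the sentence that names an ANOVA of scores as the primary analysis. An SAP cannot honour it together with the primary outcome.

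**Conclusion.** The contradiction is in the text and needs no assumption: the outcome and the powering are binary, while the named primary analysis is of scores. It should be corrected before the analysis, because as written the protocol does not say which result decides the trial, and its 80% power belongs to a test that it does not call primary.

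The practical size is illustrative only. With responder rates of 40% and 15%, normal changes and equal SD, the two candidates disagree in about 17% of trials, nearly always with the means test alone significant. If 40 and 15 are read as mean decreases, the range is from under 1% (SD 20) to 23% (SD 40). The sample size is not at fault.

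**What to change.** In the Statistical analysis section, designate one primary test: the proportion with an API reduction of at least 40% at 6 weeks, Group A versus Group C. Either of two choices resolves the contradiction:

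- the chi-square test already named; or
- a logistic or risk-difference model with the protocol's own covariates and baseline API, adding site, since randomisation is stratified by age and site and age is already listed.

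Whichever is not chosen becomes supportive. One practical point bears on the choice: at the planned rates about 0.40 × 49 + 0.15 × 49 = 27 responders are expected in the two arms, which is few for the full covariate list.

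Move the adjusted ANOVA or ANCOVA of API scores to the secondary mean-API outcomes, with the A–C, A–B and B–C contrasts at 6 and 12 weeks. Align the primary-outcome wording in the last paragraph of the introduction. State that this choice is fixed before outcomes are seen by arm.

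The cost is wording in the protocol and any SAP. No data collection changes, and the total stays at 165.

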**Methods**

Study Design

A dual-center, single-blind (examiner), parallel design randomised control trial of 165 patients attending an outpatient cardiac rehabilitation center within two public hospitals in Sydney, Australia. See **Figure 1.** for study flow diagram. The intervention populations will receive either a tablet-delivered specifically selected series of advertisement free, web-based educational videos covering multiple CVD and oral health related topics alone or partnered with individually tailored OHI. The control population will receive usual care as detailed below. The examiner will be blinded to the group allocation.

Patient population

The study population will be patients presenting to the outpatient cardiology rehabilitation centre participating in the Cardiac Education and Assessment Program (CEAP) at Westmead and Blacktown public hospitals, Sydney Australia. CEAP provides personalised support, exercise and education to help strengthen patient’s hearts after having a cardiovascular event and helps to lower risk of a future cardiovascular event (82). These patients attend due to a range of heart conditions such as coronary heart disease, heart failure, and those waiting for, or who have had a heart transplant. Due to the variety of heart conditions and co-morbidities, patients are placed on either a 6-week or 12-week program and can attend once or twice weekly. As these patients have taken part in this program, prioritising their cardiovascular health, and showing a motivation to reduce future risk of a cardiovascular event, we predict these patients will be interested in receiving education regarding oral health impacts on CVD.

Participant eligibility

A total of 165 participants will be recruited at either Westmead or Blacktown outpatient cardiac rehabilitation clinics who are attending as part of the CEAP program. Patients 18 years or older with a recent diagnosis of CVD , recent myocardial infarction and/or recent hospitalisation resulting from CVD will be approached for screening. This will include a clinical examination consisting of periodontal screening and recording (PSR), API, and sulcus bleeding index (SBI) (83) will be completed, followed by a self-report questionnaire. Patients will be excluded if:

- they have been diagnosed with heart failure.
- have/are waiting for a heart transplant,
- are too physically or mentally unwell on the day.
- have a cognitive impairment.

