- who do not speak or have limited language skills in English.

If they have visited an OHP for treatment of gum disease (supra- and/or subgingival scaling and root planning) in the last 6 months,

- have an API score of ≤59%
- are edentulous.

A study researcher will ensure that eligibility criteria are satisfied before approaching the participants by viewing their clinical records. Part of discussing the study with participants will allow the researcher to determine if they are edentulous or have seen an OHP within the last 6 months which will exclude them before the baseline assessment. A sequence of the recruitment process is provided in **Fig 2**.

Recruitment and consent

Eligible patients will be recruited either before or after their CEAP session in the cardiac rehab clinic. A trained oral health therapist will explain the study to potential participants. Electronic consent forms will be provided on iPads provided by the study, being hosted on Western Sydney Local Health District (WSLHD) Research Electronic Data Capture (REDCap) (84). As such the participant must complete written/electronic consent before being able to progress to the clinical examination (API, SBI and PSR) and data collection stage. Ethical approval will be obtained via: Western Sydney Local Health District Human Research Ethics Committee (HREC). This trial will be registered on the Australian New Zealand Clinical Trails Registry.

Randomisation

Randomisation will be stratified by age and site. A randomisation allocation table will be computer generated and REDCap will be used for allocation of participants to each group. Participants will be randomised at the end of the self-report questionnaire and randomised into a 1:1:1 ratio into one of three arms of the study. Due to the nature of the interventions within the trial, participants cannot be blinded.

Interventions

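### Randomisation is stratified by age and site, but the covariates named for the adjusted analysis include age and leave out site (minor)

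*Protocol*

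**What the plan says.** The trial recruits cardiac rehabilitation outpatients "within two public hospitals in Sydney, Australia" and allocates them 1:1:1 to three groups. On allocation, the Protocol (Methods, Randomisation) states: "Randomisation will be stratified by age and site".

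The Statistical analysis section describes the main analysis as follows: "The primary analysis will be an adjusted analysis of variance performed to assess differences between groups for API scores between baseline and follow-up". It names the adjustment terms: "Covariates used for adjusted analyses will include age, sex, highest PSR code, level of education, smoking status, and number of teeth". Shortly afterwards it adds: "Outcome measures available at baseline (PSR, SBI and API) will also be included in the statistical model". It also plans a comparison without adjustment: "An unadjusted analysis will be performed to assess differences between groups using a X^2^ test for binary (categorical) outcomes", with t-tests for continuous outcomes.

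Set side by side:

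| Stratification factor | Used in randomisation | Named in the adjusted model |
|---|---|---|
| Age | yes | yes |
| Site (two hospitals) | yes | no |

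Site is not mentioned in the subgroup list, the unadjusted tests or any other analysis sentence.

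**The concern.** Stratifying by site forces the groups to be nearly balanced within each hospital. Differences between the hospitals then largely cancel out of the treatment comparison, so the estimate varies less from trial to trial than it would under simple randomisation. A model that leaves site out does not credit this. It still counts the between-site variation as error, so its standard error is larger than the true variability of the estimate. Confidence intervals come out too wide, the test rejects less often than its nominal 5%, and precision that the design has already secured is given up.

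The loss is worth avoiding because the sample size leaves no reserve: 165 is what the planned comparison of Group A with Group C needs for 80% power, with attrition allowed for.

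**Working it through.** **Step 1: reproduce the planned sample size.** The Sample size section gives the design inputs: "This calculation includes provision for a 10% attrition rate, two tailed tests, type 1 error of 5%, and will have 80% power". For the effect it says: "we will expect to see a 40% decrease in Group A, compared to 15% in Group C". Read as responder proportions of 0.40 and 0.15, with mean 0.275, the pooled two-proportion formula without continuity correction is

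n per arm = [1.960·√(2 × 0.275 × 0.725) + 0.842·√(0.40 × 0.60 + 0.15 × 0.85)]² / (0.40 − 0.15)²

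= [1.960 × 0.6315 + 0.842 × 0.6062]² / 0.0625 ≈ 48.9, rounded up to 49.

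Allowing for attrition, 49 / 0.90 = 54.4, rounded up to 55 per arm, and 3 × 55 = 165. The stated total is reproduced exactly.

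**Step 2: cost of leaving site out.** Let R² be the share of outcome variance that site explains. The Protocol gives no value, so a range of 0 to 0.20 is assumed. With allocation stratified by site, the estimate has variance proportional to (1 − R²), while a model without site estimates the unreduced variance. Hence:

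- standard-error multiplier k = 1/√(1 − R²)
- type I error = 2·Φ(−1.960·k)
- power = Φ(1.960 + 0.842 − 1.960·k), with the effect set so that the model including site has 80% power

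For R² = 0.10, k = 1/√0.90 = 1.054 and 1.960 × 1.054 = 2.066. Type I error is 2·Φ(−2.066) = 3.9%, and power is Φ(2.802 − 2.066) = Φ(0.736) = 76.9%.

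| Assumed R² of site | SE multiplier | Type I error, site omitted | Power, site omitted |
|---|---|---|---|
| 0 | 1.000 | 5.0% | 80.0% |
| 0.01 | 1.005 | 4.9% | 79.7% |
| 0.02 | 1.010 | 4.8% | 79.4% |
| 0.05 | 1.026 | 4.4% | 78.5% |
| 0.10 | 1.054 | 3.9% | 76.9% |
| 0.20 | 1.118 | 2.8% | 72.9% |

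**Step 3: check by simulation, continuous outcome.** With 50 per arm, two equal sites and R² = 0.10, the model without site reported a mean standard error of 0.200. The actual standard deviation of the estimate was about 0.190 to 0.192. Type I error was 3.8% without site and 4.9% with it; power was 76.3% and 79.7%.

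**Step 4: check by simulation, binary outcome.** This used 50 per arm and two equal sites. Responder rates were shifted down at one site and up at the other by the amount shown. The null rate was 27.5% in both groups and the alternative was 40% against 15%.

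| Site shift | Type I error: plain χ² / Mantel-Haenszel | Power: plain χ² / Mantel-Haenszel |
|---|---|---|
| 0 | 5.0% / 5.1% | 81.8% / 81.8% |
| ±5 points | 5.0% / 5.2% | 81.7% / 82.0% |
| ±10 points | 4.3% / 4.8% | 82.6% / 84.1% |
| ±14 points | 4.0% / 5.0% | 83.4% / 86.3% |

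Under the null, a shift of g corresponds to R² = g²/(0.275 × 0.725). That is 0.01/0.199 = 0.05 for ±10 points and 0.0196/0.199 = 0.10 for ±14 points. The formula in step 2 predicts 4.4% and 3.9% there, close to the simulated 4.3% and 4.0%.

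**The case against.** The strongest reply is that the Protocol does not exclude site. Its list is worded as what the covariates will include, further terms are added two sentences later, and the section opens by saying that the statistical plan is still to be determined. This stands in part: a reader might infer that site has been ruled out, and the text does not support that. But the Protocol goes beyond leaving the model open. It names nine terms and carries over one of its two stratification factors, so someone following the text would fit a model without site.

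The second reply is that site may matter little. Both hospitals run the same rehabilitation programme, and a single calibrated, blinded examiner does all assessments (Methods, Interventions), which limits measurement differences between sites. This also stands. It does not remove possible differences in patient mix, but it makes large values of R² hard to defend from the document.

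The third reply is that an unadjusted test ignores the strata by definition. That is fair, and labelling such a test as unadjusted is no error. The recommendation to stratify it applies only where the binary endpoint is tested for the primary comparison.

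A reader might also go further and infer that the covariate list would overload a logistic model of the responder endpoint and distort its odds ratio. The Protocol names no logistic model; it names an adjusted analysis of variance and an unadjusted χ² test. Nor does naming PSR in two sentences amount to a defect: the mentions can be read as the same variable, and a duplicated term would leave the treatment estimate unchanged.

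**Conclusion.** The mismatch is real and minor. The named covariates keep age and omit site, although both define the randomisation strata. If site is prognostic, the consequence is standard errors that are somewhat too large and a conservative test. A reader might infer that ignoring a stratification factor produces false positives; the calculation shows the reverse, with type I error at or below 5%.

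For an assumed site R² up to 0.10, the loss is 0 to about 3 power points; at 0.20 it is about 7. If site explains nothing, nothing is lost. These figures measure the loss against a site-adjusted analysis with 80% power. They do not show that the trial must fall below its target: in the binary simulation with the planned rates held fixed, the plain χ² test stayed above 80%, and using site added 1.5 points at a ±10-point shift (84.1% against 82.6%). The simulations assume two equal sites, and the Protocol gives neither the site split nor the site effect. The omission is certain from the text; its size is not.

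**What to change.** In the Protocol's Statistical analysis section, add site (two levels) to the covariates of the adjusted models, next to age. Wherever the binary responder endpoint is tested for the primary comparison of Group A with Group C, use a Mantel-Haenszel test stratified by site in place of the plain χ² test. The other named covariates can stay as they are.

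The cost is a short change of wording and one degree of freedom. Site is already known for every participant at randomisation, so no new data are needed, and the total of 165 does not change. The change should be made before allocation is unmasked for analysis, so that it cannot look like a choice made after seeing the results.
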